#### **Chronic concomitant Medications**

Medication that has been:

prescribed or over the counter (OTC) that has been taken or will continue to be taken regularly for at least a period of 6 months, or

is required to be taken indefinitely by the patient, or

prescribed or OTC that has been taken multiple times (each time for at least 6 months)

#### **Chronic Occlusion**

An occlusion presumed to have been present for at least one month prior to the procedure.

- Total Occlusion:
- An occlusion with no ante grade filling of contrast to the distal segment (TIMI grade 0)
- Sub-total Occlusion:
- TIMI grade I, and with collateral filling of the distal segment

#### **Clinically-indicated Target Lesion Revascularization (CI-TLR):**

In the patient cohorts assigned to clinical follow-up only (such as the SPIRIT WOMEN Single Arm Study), all revascularizations are considered clinically indicated.

A revascularization is clinically indicated if angiography at follow-up shows a percent diameter stenosis  $\geq 50\%$  (QCA assessment) **and** if one of the following occurs:

1. A positive history of recurrent angina pectoris presumably related to the target vessel.
2. Objective signs of ischemia at rest (ECG changes) or during exercise test (or equivalent) presumably related to the target vessel.

3. Abnormal results of any invasive functional diagnostic test (e.g. Doppler flow velocity reserve, fractional flow reserve). The results of the test must be documented in the Case Report Form.

A TLR with a diameter stenosis  $\geq 70\%$  (QCA) in the absence of the above mentioned ischemic signs or symptoms is also considered clinically indicated.

Comment: clinically indicated is a documented, provisional decision to re-intervene based on clinical symptoms and/or results of non invasive functional testing, before any coronary imaging. These criteria are intended to determine clinical indications for reintervention in patients undergoing routine angiographic follow-up. In the patient cohorts assigned to clinical follow-up only, or in studies without routine angiographic follow-up, all revascularizations are considered clinically indicated.

**Not Clinically indicated** TLRs are reinterventions for:

1. all stenoses  $< 50\%$  in the presence or absence of ischemic signs or symptoms;
2. all stenoses  $\geq 50\%$  but  $< 70\%$  without ischemic signs or symptoms.

#### **Clinically-indicated Target Vessel Revascularization (CI-TVR):**

In the patient cohorts assigned to clinical follow-up only (such as the SPIRIT WOMEN Single Arm Study), all revascularizations are considered clinically indicated.

A revascularization is clinically indicated if angiography at follow-up shows a percent diameter stenosis  $\geq 50\%$  (QCA assessment) and if one of the following occurs:

1. A positive history of recurrent angina pectoris presumably related to the target vessel.
2. Objective signs of ischemia at rest (ECG changes) or during exercise test (or equivalent) presumably related to the target vessel.
3. Abnormal results of any invasive functional diagnostic test (e.g. Doppler flow velocity reserve, fractional flow reserve). The results of the test must be documented in the Case Report Form.

A TVR with a diameter stenosis  $\geq 70\%$  (QCA) in the absence of the above mentioned ischemic signs or symptoms is also considered clinically indicated.

**Not Clinically indicated** TVRs are reinterventions for:

1. all stenoses  $< 50\%$  in the presence or absence of ischemic signs or symptoms;
2. all stenoses  $\geq 50\%$  but  $< 70\%$  without ischemic signs or symptoms.

#### **Coronary Artery Bypass Graft Surgery (CABG)**

- Acute CABG is defined as immediate transfer from the cath lab to the operative room for emergent bypass surgery during the initial treatment phase.
- CABG during follow-up is only considered as a Clinical-indicated Target Lesion Revascularization if coronary angiography indicates a diameter of stenosis  $\geq 50\%$  of the stented coronary segment associated with one of the following conditions:
  1. A positive history of recurrent angina pectoris presumably related to the target vessel.
  2. Objective signs of ischemia at rest (ECG changes) or during exercise test (or equivalent) presumably related to the target vessel.
  3. Abnormal results of any invasive functional diagnostic test (e.g. Doppler flow velocity reserve, fractional flow reserve). The results of the test must be documented in the Case Report Form.

## **Death**

Death defined by the Academic Research Consortium is as follows:

All death is considered to be cardiac death unless an unequivocal noncardiac cause can be established. Specifically, any unexpected death even in patients with coexisting potentially fatal noncardiac disease (eg, cancer, infection) should be classified as cardiac.

### **Cardiac death**

Any death due to proximate cardiac cause (eg, myocardial infarction, low-output failure, fatal arrhythmia), unwitnessed death and death of unknown cause, and all procedure-related deaths, including those related to concomitant treatment, will be classified as cardiac death.

### **Vascular death**

Death caused by noncoronary vascular causes, such as cerebrovascular disease, pulmonary embolism, ruptured aortic aneurysm, dissecting aneurysm, or other vascular diseases.

### **Non-cardiovascular death**

Any death not covered by the above definitions, such as death caused by infection, malignancy, sepsis, pulmonary causes, accident, suicide, or trauma.

## **Device Malfunction**

A malfunction is a failure of a device to meet its performance specifications or otherwise perform as intended. Performance specifications include all claims made in the labeling of the device. The intended performance of a device refers to the intended use for which the device is labeled or marketed.

## **Dissection**

### ***National Heart, Lung, and Blood Institute (NHLBI) Dissection Classification System:***

- A.** Minor radiolucencies within the lumen during contrast injection with no persistence after dye clearance.
- B.** Parallel tracts or double lumen separated by a radiolucent area during contrast injection with no persistence after dye clearance.
- C.** Extraluminal cap with persistence of contrast after dye clearance from the lumen.
- D.** Spiral luminal filling defects.
- E.** New persistent filling defects.
- F.** Non-A-E types that lead to impaired flow or total occlusion.

**Note:** Type E and F dissections may represent thrombus.

## **Hematoma**

Hemorrhagic event requiring transfusion, prolongation of hospitalization or an intervention.

## **In-Stent**

Within the margins of the stent.

## **In-Segment**

Within the margins of the stent and 5 mm proximal and 5 mm distal to the stent.

## **Intent To Treat (ITT) Population**

The intent-to-treat population for the randomized sub-study will consist of all patients (all lesions) randomized, regardless of the treatment actually received. Subjects will be analyzed in the treatment arm to which they were randomized.

Analysis for the Single Arm Study will be performed on the intent-to-treat population which will include all patients:

1. who have signed the Patient Informed Consent
  2. who have been registered in the ICON IVRS system
- AND
3. who comply to at least one of the following:
    - a. at least one XIENCE V EECS has been implanted
    - b. a non-XIENCE V EECS has been implanted after an intention to or an attempt made to implant a XIENCE V EECS
    - c. no stent was implanted after an intention to or an attempt made to implant a XIENCE V EECS

Lesions for which there was no attempt to implant a XIENCE V EECS and lesions located in a bypass graft will not be considered in the analysis for the Single Arm Study.

For the pooled analysis the intent-to-treat population will consist of the intent-to-treat population in the SPIRIT WOMEN Single Arm Study and patients from the intent-to-treat population in the randomized sub-study who were randomized to XIENCE EECS.

#### **Late Loss (LL)**

General definition: Calculated as MLD post-procedure – MLD at follow-up

- **In-segment Late Loss:** in-segment MLD post-procedure – in segment MLD at follow-up
- **In-stent Late Loss:** in-stent MLD post-procedure – in-stent MLD at follow-up
- **Proximal Late Loss:** proximal MLD post-procedure – proximal MLD at follow-up (proximal defined as within 5 mm proximal to stent placement)
- **Distal Late Loss:** distal MLD post-procedure – distal MLD at follow-up (distal defined as within 5 mm distal to stent placement)

#### **Major Epicardial Vessels**

Left anterior descending artery (LAD) with septal and diagonal branches;

Left circumflex artery (LCX) with obtuse marginal and/or ramus intermedius branches;

Right coronary artery (RCA) and any of its branches.

#### **Metabolic Syndrome**

Metabolic syndrome, (also, syndrome x, insulin resistance syndrome) is a combination of medical disorders that affect a large number of people. If you have three or more of the following five conditions, you are diagnosed as metabolic syndrome:

- Increased waist circumference ( $\geq 102$  cm in men and  $\geq 88$  cm in women), indicating central obesity
- Elevated triglycerides ( $\geq 150$  mg/dL or 1.7 mmol/l)
- Decreased HDL cholesterol ( $< 40$  mg/dL for men,  $< 50$  mg/dL for women)
- Blood pressure above 130/85 or active treatment for hypertension
- Glucose levels above 100 mg/dL (a symptom of diabetes)

#### **Minimum Lumen Diameter (MLD)**

The average of two orthogonal views (when possible) of the narrowest point within the area of assessment – in lesion, in stent or in segment. MLD is visually estimated during angiography by the Investigator; it is measured during QCA by the Angiographic Core Lab.

## Myocardial Infarction (MI)

Myocardial Infarction Classification and Criteria for Diagnosis is defined by the Academic Research Consortium as follows:

| Classification      | Biomarker Criteria*                                                                           | Additional Criteria                                                                                                                                               |
|---------------------|-----------------------------------------------------------------------------------------------|-------------------------------------------------------------------------------------------------------------------------------------------------------------------|
| Periprocedural PCI  | Troponin > 3 x URL or CK-MB > 3 x URL                                                         | Baseline value <URL                                                                                                                                               |
| Periprocedural CABG | Troponin > 5 x URL or CK-MB > 5 x URL                                                         | Baseline value <URL and any of the following: new pathologic Q waves or LBBB, new native or graft vessel occlusion, imaging evidence of loss of viable myocardium |
| Spontaneous         | Troponin > URL or CK-MB > URL                                                                 |                                                                                                                                                                   |
| Sudden death        | Death before biomarkers obtained or before expected to be elevated                            | Symptoms suggestive of ischemia and any of the following: new ST elevation or LBBB, documented thrombus by angiography or autopsy                                 |
| Reinfarction        | Stable or decreasing values on 2 samples with a 20% increase 3 to 6 hours after second sample | If biomarkers increasing or peak not reached then insufficient data to diagnose recurrent MI                                                                      |

URL = Upper Reference Limit (defined 99th percentile of normal reference range);

LBBB = Left Bundle-branch Block

\* Baseline biomarker value requiring before study procedure and presumes a typical rise and fall

- **Periprocedural MI After PCI**

The periprocedural period includes the first 48 hours after percutaneous coronary intervention.

- **Periprocedural MI After CABG**

The periprocedural period includes the first 72 hours after coronary artery bypass CABG grafting.

- **Spontaneous MI**

MI after the periprocedural period may be secondary to late stent complications or progression of native disease.

Performance of ECG and angiography supports adjudication to either a target or non-target vessel in most cases.

With the unique issues and pathophysiological mechanisms associated with these later events as well as the documented adverse impact on short-and long-term prognosis, a more sensitive definition than for periprocedural MI of any elevation of troponin above the upper range limit is used. All late events that are not associated with a revascularization procedure simply as spontaneous.

- **Electrocardiographic Classification**

Within this category Q-wave MI and Non Q-wave MI are distinguished as follows:

- Q-wave MI: Development of new pathologicals in 2 or more contiguous leads (according to the Minnesota code or Novacode) with or without post-procedure CK or CK-MB levels elevated above normal.

- Non Q-wave MI: All MIs not classified as Q-wave.

- **Relation to the Target Vessel**

All infarcts that cannot be clearly attributed to a vessel other than the target vessel will be considered related to the target vessel.

**No-reflow**

An acute reduction in coronary flow (TIMI grade 0-1) in the absence of dissection, thrombus, spasm, or high-grade residual stenosis at the original target lesion. Also see 'Acute Closure'.

**Percent Diameter Stenosis**

The value calculated as  $100 * (1 - \text{MLD/RVD})$  using the mean values from two orthogonal views (when possible) by QCA.

**Percutaneous Coronary Intervention (PCI)**

Refers to all interventional cardiology methods for treatment of coronary artery disease.

**Persisting Dissection**

Dissection at follow-up that was present post-procedure.

**Planned Staged Procedure**

A planned staged procedure is defined as the treatment of baseline lesions during additional cardiac catheterization procedures following the index procedure. The definition is limited to procedures that are planned during/prior to index procedure. If worsening/exacerbation of patient condition occurs at the time of staged procedure or leads to rescheduling of the staged procedure, or a new clinical condition occurs during the staged procedure, the condition should be reported as an adverse event. The treatment of the baseline lesions at staged procedure will not be considered as a revascularization.

**Q-wave Myocardial Infarction (QMI)**

Development of new pathological Q waves in 2 or more contiguous leads (according to the Minnesota Code as assessed by the ECG core laboratory) with or without post-procedure CK or CK-MB levels elevated above normal.

**Reference Vessel Diameter (RVD)**

An approximation of the diameter of the vessel at the location of the target lesion. RVD is visually estimated during angiography by the Investigator and it is measured during QCA by the Angiographic Core Laboratory

**Restenosis**

Re-narrowing of the artery following the removal or reduction of a previous narrowing.

**Revascularization:**

Revascularization is defined by the Academic Research Consortium^28 as follows:

- **Target Lesion Revascularization (TLR)**

Target lesion revascularization is defined as any repeat percutaneous intervention of the target lesion or bypass surgery of the target vessel performed for restenosis or other complication of the target lesion. All target lesion revascularizations should be classified prospectively as clinically indicated\* or not clinically indicated by the investigator prior to repeat angiography. An independent angiographic core laboratory should verify that the severity of percent diameter stenosis meets requirements for clinical indication and will overrule in cases where investigator reports are not in agreement. The target lesion is defined as the treated segment from 5 mm proximal to the stent and to 5 mm distal to the stent.

- **Target Vessel Revascularization (TVR)**

Target vessel revascularization is defined as any repeat percutaneous intervention or surgical bypass of any segment of the target vessel. The target vessel is defined as the entire major coronary vessel proximal and distal to the target lesion, which includes upstream and downstream branches and the target lesion itself.

- **Non Target Lesion Revascularization (non-TLR)**

Any revascularization in a lesion other than the target lesion is considered a non target lesion revascularization.

- **Non Target Vessel Revascularization (non-TVR)**

Any revascularization in a vessel other than the target vessel is considered a non-target vessel revascularization.

**\*Clinically indicated revascularization**

A revascularization is considered clinically indicated if angiography at follow-up shows a percent diameter stenosis  $\geq 50\%$  (core laboratory quantitative coronary angiography assessment) and if one of the following occurs:

- (1) A positive history of recurrent angina pectoris, presumably related to the target vessel;
- (2) Objective signs of ischemia at rest (ECG changes) or during exercise test (or equivalent), presumably related to the target vessel;
- (3) Abnormal results of any invasive functional diagnostic test (eg, Doppler flow velocity reserve, fractional flow reserve);
- (4) A TLR or TVR with a diameter stenosis  $\geq 70\%$  even in the absence of the above-mentioned ischemic signs or symptoms.

**Serious Adverse Device Effect**

Adverse device effect that has resulted in any of the consequences characteristic of a serious adverse event or that might have led to any of these consequences if suitable action had not been taken or intervention had not been made or if circumstances had been less opportune.

**Serious Adverse Event (SAE)**

Adverse event that:

- led to death,
- led to a serious deterioration in the health of the patient that:
  - resulted in a life-threatening illness or injury,
  - resulted in a permanent impairment of a body structure or a body function,
  - required in-patient hospitalization or prolongation of existing hospitalization
  - resulted in medical or surgical intervention to prevent permanent impairment to body structure or a body function
- led to fetal distress, fetal death or a congenital abnormality or birth defect

**Stent Thrombosis**

Stent thrombosis is defined and discussed by the Academic Research Consortium as follows:

Stent thrombosis should be reported as a cumulative value at the different time points and with the different separate time points.

Time 0 is defined as the time point after the guiding catheter has been removed and the subject left the catheterization laboratory.

### **Timing**

|                                         |                                            |
|-----------------------------------------|--------------------------------------------|
| Acute stent thrombosis *     | 0-24 hours post stent implantation         |
| Subacute stent thrombosis *  | > 24 hours-30 days post stent implantation |
| Late stent thrombosis †      | > 30 days-1 year post stent implantation   |
| Very late stent thrombosis † | > 1 year post stent implantation           |

\* Acute/subacute can also be replaced by early stent thrombosis. Early stent thrombosis (0-30 days) –*this definition is currently used in the community.*

† Including “primary” as well as “secondary” late stent thrombosis; “secondary” late stent thrombosis is a stent thrombosis after a target segment revascularization.

### **Stent Thrombosis Categories: a) Definite b) Probable, and c) Possible**

#### **a) Definite stent thrombosis**

Definite stent thrombosis is considered to have occurred by either angiographic or pathologic confirmation.

##### **Angiographic confirmation of stent thrombosis\***

The presence of a thrombus† that originates in the stent or in the segment 5 mm proximal or distal to the stent and presence of at least 1 of the following criteria within a 48-hour time window:

- Acute onset of ischemic symptoms at rest
- New ischemic ECG changes that suggest acute ischemia
- Typical rise and fall in cardiac biomarkers (refer to definition of spontaneous MI)
- Nonocclusive thrombus
  - Intracoronary thrombus is defined as a (spheric, ovoid, or irregular) noncalcified filling defect or lucency surrounded by contrast material (on 3 sides or within a coronary stenosis) seen in multiple projections, or persistence of contrast material within the lumen, or a visible embolization of intraluminal material downstream.
- Occlusive thrombus
  - TIMI 0 or TIMI 1 intrastent or proximal to a stent up to the most adjacent proximal side branch or main branch (if originates from the side branch).

\*The incidental angiographic documentation of stent occlusion in the absence of clinical signs or symptoms is not considered a confirmed stent thrombosis (silent occlusion).

†Intracoronary thrombus.

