### **5.2 Secondary Endpoints**

The following secondary endpoints will be examined:

Acute Success (Clinical Device Success and Clinical Procedure Success)

Adjudicated Stent Thrombosis at 30 days, 240 days and at 1, 2, 3, 4 and 5 years (Definite, Probable, Possible)

Adjudicated revascularization (TLR/TVR/all revascularizations) at 30 days, 240 days and at 1, 2, 3, 4 and 5 years

Adjudicated Composite rate of Cardiac Death, MI attributed to the target vessel and CI-TLR at 30 days, 240 days and at 1, 2, 3, 4 and 5 years.

Adjudicated Composite rate of all Death, all MI and Target Vessel Revascularization (TVR) at 30 days, 240 days and at 2, 3, 4 and 5 years.

Adjudicated Composite rate of all Death, all MI and any Revascularization (TLR/TVR/non TVR) at 30 days, 240 days and at 1, 2, 3, 4 and 5 years.

Adjudicated Cardiac Death, Non-Cardiovascular Death, Vascular Death, Q-wave MI and Non Q-wave MI (Peri-Procedural, Unrelated to PCI) at 30 days, 240 days and at 1, 2, 3, 4 and 5 years.

In-stent Late Loss (LL) at 270 days (*main* secondary endpoint for the randomized sub-study)

In-segment Late Loss (LL) at 270 days (for the randomized sub-study)

In-stent and in-segment Angiographic Binary Restenosis rates at 270 days (randomized sub-study)

In-stent and in-segment percent Diameter Stenosis at 270 days (randomized sub-study)

Aneurysm, thrombus and persisting dissection at 270 days (for the randomized sub-study)

Additional analysis of specific female demographics such as menopausal, hysterectomy and oophorectomy status, past and current use of hormonal contraceptives, and use of weak estrogens will be outlined in the Statistical Analysis Plan (SAP).

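### Two descriptions of thrombus sit in the list of confirming criteria for definite stent thrombosis, so a silent non-occlusive thrombus counts as definite and the rule conflicts with its own footnote on silent occlusion

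*Protocol*

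**What the plan says.** Protocol, Appendix II, Angiographic confirmation of stent thrombosis, sets two conditions: a thrombus originating in the stent or within 5 mm of either end, and "presence of at least 1 of the following criteria within a 48-hour time window". The list then has five bullets at the same level:

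1. "Acute onset of ischemic symptoms at rest"
2. "New ischemic ECG changes that suggest acute ischemia"
3. "Typical rise and fall in cardiac biomarkers (refer to definition of spontaneous MI"
4. Non-occlusive thrombus, with the sub-text "Intracoronary thrombus is defined as a (spheric, ovoid, or irregular) noncalcified filling defect or lucency surrounded by contrast material" and further morphological detail
5. Occlusive thrombus, with the sub-text "TIMI 0 or TIMI 1 intrastent or proximal to a stent up to the most adjacent proximal side branch or main branch"

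Two footnotes belong to the rule. The asterisk, attached to its heading, says: "The incidental angiographic documentation of stent occlusion in the absence of clinical signs or symptoms is not considered a confirmed stent thrombosis (silent occlusion". The dagger, attached to the word thrombus in the lead sentence, gives only the term intracoronary thrombus and no definition.

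Section 5.2 makes adjudicated stent thrombosis (definite, probable, possible) a secondary endpoint at 30 days, 240 days and 1 to 5 years. It lists separately "Aneurysm, thrombus and persisting dissection at 270 days (for the randomized sub-study". Section 8.2 schedules angiography at 270 ± 14 days for the sub-study of about 450 patients; the Single Arm Study has no routine film. Section 8.6.1 has the Clinical Events Committee (CEC) adjudicate according to the Appendix II definitions.

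**The concern.** The second condition is there to require clinical evidence in addition to the film. Bullets 4 and 5 add none: they say what the thrombus in the first condition looks like. With them in the list, the required thrombus can serve as its own confirmation.

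At stake is the boundary between a clinical safety event and an imaging finding. Asymptomatic thrombus is most likely to be seen on a protocol-mandated film, and only the sub-study has one. If some silent findings are adjudicated as definite, stent thrombosis rates in the sub-study and the Single Arm Study no longer measure the same thing, although Sections 9.2 and 9.3.1 pool the XIENCE patients of both parts. Two adjudicators could also classify the same film differently and both cite Appendix II.

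**Working it through.** No sample size or power figure is in dispute, so the check is a reading of the rule followed by simple proportions.

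**The rule as laid out.** Let T be a thrombus in or within 5 mm of the stent, and C1 to C5 the five bullets. The rule is: definite if T and (C1 or C2 or C3 or C4 or C5), subject to the asterisk footnote. C4 and C5 restate T by type.

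| Finding | Bullets | Asterisk footnote | Result as written |
|---|---|---|---|
| Thrombus with symptoms, ECG change or biomarkers | C1, C2 or C3 met | does not apply | definite on any reading |
| Silent occlusion | C5 met | excludes it | list and footnote conflict; the footnote, as the express exception, removes it |
| Silent non-occlusive thrombus | C4 met | names occlusion only | definite stent thrombosis |

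**Is it an artefact of text extraction?** The Version 2.0 column of the revision history (Appendix VIII) carries the same five-bullet list, so that is unlikely.

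**Which reports are affected?** The earliest scheduled film is at 270 − 14 = 256 days. The 240-day contact closes at 240 + 14 = 254 days. A finding on an on-schedule film would therefore enter the cumulative rates from 1 year onward, not the 30-day or 240-day rates.

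**Size per case.** Section 9.2 plans about 300 XIENCE and 150 CYPHER patients in the sub-study, and about 1850 XIENCE patients in the pooled analysis.

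- One case in 300: 1/300 = 0.33 percentage points
- One case in 150: 1/150 = 0.67 percentage points
- One case in 1850: 1/1850 = 0.05 percentage points

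**Background for scale.** Section 2.1.1 cites a 1-year cumulative definite or probable rate of 0.66% in an earlier XIENCE V registry. Applied here as an assumption, it gives 0.0066 × 300 = 2.0 and 0.0066 × 150 = 1.0 expected events, or about 3 in 450. One added case is therefore not small beside the expected count in either arm.

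**What cannot be computed.** The documents give no frequency of incidental non-occlusive thrombus at 270 days, so the number of cases is unknown and may be zero.

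**The case against.** The strongest reply is that the intended meaning can be recovered from the same text. The sub-text of bullet 4 is openly a definition. The dagger points to the term that bullet 4 defines. A 48-hour window makes sense for symptoms, ECG changes and markers but not for a type of thrombus. The asterisk footnote makes sense only if clinical signs are required. On this view it is a layout slip that an independent committee of cardiologists would read through. All of this stands as evidence of intent. It does not cure the text, because Section 8.6.1 sends the committee to the Appendix II wording and, for silent non-occlusive thrombus, nothing in that wording excludes the case.

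A reader might go further and infer that every thrombus seen on film confirms itself, so that all incidental 270-day findings become definite events. The documents do not support that, because the asterisk footnote removes silent occlusion. A reader might also infer that the reported rate would be roughly doubled overall. That needs a frequency of incidental findings, which the documents do not give.

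It is also fair to say that both randomized arms have the film, so the ambiguity applies to XIENCE and CYPHER alike, and that no formal comparison between the sub-study and the Single Arm Study is planned. Nor is overlap between secondary endpoints a fault in itself. These points limit the consequence but do not remove it.

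**Conclusion.** The point holds in a limited form. As written, the rule classes a silent non-occlusive thrombus as definite stent thrombosis, and for silent occlusion its list contradicts its footnote. This is an error of list layout in an endpoint definition, not a deliberate choice of rule.

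The effect is 0.33 points per case in the XIENCE arm, 0.67 in the CYPHER arm and 0.05 in the pooled XIENCE group, taking the planned numbers as denominators. The number of cases is unknown. The measure affected is a secondary endpoint that Section 9.4 treats descriptively. The primary composite of death, MI and TVR, and the late-loss non-inferiority test on which the sub-study's success rests, do not use this definition. The correction should be made because it is free and removes a real ambiguity in adjudication, not because it threatens the main conclusions.

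**What to change.** In Appendix II, move the non-occlusive and occlusive thrombus descriptions out of the criteria list and place them under the dagger footnote as the definition of intracoronary thrombus. Leave three qualifying criteria: ischemic symptoms at rest, new ischemic ECG changes, and a typical rise and fall in biomarkers.

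A silent non-occlusive thrombus on the 270-day film then meets no qualifying criterion and is reported only under the separate 270-day angiographic thrombus endpoint. The asterisk footnote agrees with the list and need not be extended.

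The cost is the re-layout of one definition, a note to the CEC, and the same edit wherever its working documents copy the text. If adjudication has begun, any angiographically confirmed case resting on bullet 4 or 5 alone should be looked at again. No new data, visits or analyses are required.
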